### Study partners

Three frontline harm reduction agency partners—Parkdale Queen West Community Health Centre (Queen West site), South Riverdale Community Health Centre, and The Works at Toronto Public Health—have been funded as DCS intake sites. With the exception of The Works, which is a public health agency, the remaining two partnering frontline agencies are community health centers, and all agencies combine harm reduction service delivery with access to other services, including primary care, mental health care, and social service programs. As DCS intake sites, agencies will collect drug samples from participants, administer intake and post-test surveys, facilitate transport of samples to clinical laboratories, and communicate analysis results to participants along with relevant harm reduction information. Notably, Parkdale Queen West Community Health Centre (Queen West site) also houses TRIP Project, a program providing information and resources on harm reduction and safer sex to youth in nightlife and party settings.

Clinical laboratory partners at the Centre for Addiction and Mental Health and St. Michael's Hospital—two urban hospitals with specialized programs for substance use—will analyze samples of drugs from participants at frontline harm reduction agencies using LC- and GC-MS techniques and guide the aggregation of analysis data across sites to identify composition (qualitative and quantitative) trends in the unregulated drug supply.

To bolster the relevance of findings and ensure effective knowledge translation strategies that address the needs of key populations, a Community Advisory Board made up of people who use drugs will advise on all aspects of the design, analysis, interpretation, and knowledge translation activities of this study [39]. Additionally, protocols for research methods and outcome measures will be aligned as much as possible with DCS implemented in other Canadian jurisdictions, including British Columbia and the capital city of Ottawa, Ontario, to maximize the potential comparability of findings across distinct settings.

### Data collection

#### Intake and post-test surveys (Aim 1)

Intake and post-test surveys will be administered to all consenting DCS clients at the three sites in Toronto, including participants who access DCS once and those who access DCS multiple times, allowing for a combined use of cross-sectional and longitudinal approaches. Surveys will be administered by frontline staff on an electronic tablet with the option for self-administration depending on the needs of the participant. Guided by the abovementioned conceptual framework, demographic and drug-using factors will be collected at first visit to DCS via a baseline intake survey to assess the influence of additional vulnerabilities facing key populations. An anonymous identifier will be created in the baseline intake survey and linked to intake surveys completed at subsequent visits. Questions on the intake survey, administered at every visit to DCS, include the following: What substance participants believe they are having tested?; When and where they purchased the substance?; and, If they are sharing the results with others, with how many people? Post-test surveys conducted immediately after analysis results are provided will query participants about their intended behaviors in response to analysis results, as well as allow frontline staff to record other services accessed (e.g., SCS, naloxone) and observed behaviors (e.g., discarding remainder of drug that was tested).

#### Sample size (Aim 1)

In lieu of randomization, which is neither feasible nor ethical given the type of service to be examined in the present study, a community recruitment model will be employed whereby a survey of all consenting DCS clients is undertaken (i.e., the sampling frame consists of all clients of DCS). Since study participants are recruited “passively” through their use of the service, we are unable to estimate the proportion of surveys to be obtained from unique versus repeat clients until after DCS are implemented. We therefore cannot determine the total person-time data that will be collected. We note, however, that 75% of feasibility survey respondents recruited from frontline agencies reported being willing to access DCS. The total population of structurally vulnerable people who use drugs in Toronto is estimated at 9000, among whom 20% are willing to use SCS [35]; it is estimated that *n* = 1800 unique individuals who use drugs access frontline agencies. Previous literature suggests social desirability bias in reports of willingness to access harm reduction services [40]; we therefore estimate an approximate total of *n* = 1080 DCS clients.

#### SCS client survey data (Aim 1 substudy)

An ongoing longitudinal cohort is collecting data from people who inject drugs who do and do not use SCS at the three frontline agencies participating in the DCS network. This allows for harmonization of survey tools across both projects. As such, for participants consenting to linkages, data from a standardized SCS cohort survey (e.g., age, gender, neighborhood of residence, and drug-using factors) and data from the SCS pre/post injection assessment form (e.g., overdose outcomes, whether emergency medical attention was provided [i.e., SCS staff response and/or call to 911 for paramedic response], naloxone administered) will be accessible for consenting participants. This will also allow for a substudy consisting of a comparison of outcomes (i.e., overdose incidence and related risk behaviors) among frontline agency clients who access SCS exclusively, who access both SCS and DCS, and who access neither.

#### Qualitative interviews (Aim 2)

In-depth interviewing will investigate participant perceptions of the contexts, facilitators, and barriers to the use of DCS and its capacity to influence overdose risk. We will also specifically investigate participant perspectives on the influence of gender on both DCS access and overdose risk, given the lack of data on this topic and the known contribution of gender to drug-related harms (i.e., women are less likely to manage illegal drug acquisition and inject themselves compared with men) [41–44]. We will employ purposive sampling to achieve gender diversity (including transgender individuals) and to ensure youth representation drawn from Toronto’s structurally vulnerable drug-using population [35]. Two interview waves will be conducted, and both will include 10 interviews with participants from each of the three SCS/DCS sites, which includes 5 interviews with youth accessing DCS via the TRIP Project (total *n* per wave = 30; total *n* = 60). Two waves of interviews will also be held with institutional stakeholders providing DCS services (*n* = 10 per wave; *n* = 20) to provide insight into the capacity and limits of DCS to prevent overdose and related risk behaviors.

#### Analysis of drug samples (Aim 3)

Mass spectrometry (MS) is a versatile technology that in combination with liquid (LC)- or gas (GC)-chromatographic techniques can identify virtually any chemical compound [45]. There are various MS instrument configurations, but essentially MS allows for highly accurate identification of a compound by measuring its mass to charge ratio (m/z) and analyzing its fragmentation pattern (mass spectrum) [29]. Separation of compounds is accomplished through the use of LC- or GC-columns. Importantly, LC- and GC-MS methods can distinguish between structural and/or functional analogs and can therefore identify the presence of highly potent toxic opioids such as fentanyl and its analogs within samples that contain multiple opioids [3, 46–48]. Drug samples will be transported to nearby clinical laboratories for analysis with LC- and GC-MS. Analysis results on composition (qualitative and quantitative) of drug samples will be communicated within one to two business days to frontline staff, although the ultimate goal of the pilot project is to reduce turnaround time to < 2 h; this evaluation will seek to identify process refinements that may expedite faster analysis and dissemination of results. Frontline staff will communicate results along with tailored harm reduction strategies to clients either in person or by phone.

#### Coroner and paramedic services (Aim 3)

Data-sharing agreements with the Office of the Chief Coroner for Ontario (OCC) and Toronto Paramedic Services (TPaS) will cover both de-identified individual- and aggregated-population level data on the incidence of fatal and non-fatal overdose events, including toxicology, temporal information, and geographic locations.

#### Estimated overdose incidence (Aim 3)

While no formal estimates of the overdose rate among people who use drugs in Toronto have been derived, 1002 overdose calls (fatal and non-fatal combined) were made to Toronto Paramedic Services between January 2018 and December 2018 in neighborhoods adjacent to the three frontline DCS sites, representing 31% of all calls across Toronto [49]; these neighborhoods are also those with the greatest density of people who use drugs [35]. We also note that the incidence of > 1000 overdose events recorded near DCS sites implies a relatively high event rate among potential DCS clients.

### Analytic plan

#### Multivariable model of participant overdose risk behaviors (Aim 1)

For participant survey binary outcomes, we will employ either population-averaged models (i.e., generalized estimating equations; GEE) or subject-specific models (generalized linear mixed models; GLMM) with binomial distribution and logit link. The primary outcome is recent (i.e., past 6 months) self-reported overdose; the primary exposure is a categorical measure of frequency of DCS access over the past 6 months. GEE will be used if participant visits are equally distributed over time and if we have low levels of missing data. In the case of unequal distribution of participant visits over time and/or substantial missing data, we will employ GLMM. These models efficiently address problems of missing data and variable timing of subject visits. Both GEE and GLMM are suited to the analysis of longitudinal data, as they can account for both within-subject correlation and between-subject differences with results also remaining highly interpretable. We will initially model temporal correlations between subject responses using an autoregressive structure, with subject-specific variances and correlations assumed to decline exponentially over time; this is critical given that we anticipate variance in client follow-up times. GLMM models will also include independent time-varying variables from the linked intake and post-test surveys as potential confounders. This will allow for a “pre versus post” test evaluation using longitudinal DCS data. To assess potential bias as a result of loss to follow-up, sociodemographic and drug-related factors collected on the intake and post-test surveys will be compared among participants who only completed a baseline DCS visit and those that accessed the service repeatedly. Multilevel multiple imputations may also be considered if needed.

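### Aim 1 lets visit spacing and missingness choose between two different odds ratios, and its claim that the models deal with visit timing needs an assumption that the design makes doubtful

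*Protocol article*

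**What the plan says.** All of this is in the Protocol article, mainly under *Multivariable model of participant overdose risk behaviors (Aim 1)*.

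- **Candidate models:** "we will employ either population-averaged models (i.e., generalized estimating equations; GEE) or subject-specific models (generalized linear mixed models; GLMM) with binomial distribution and logit link".
- **Rule for choosing:** "GEE will be used if participant visits are equally distributed over time and if we have low levels of missing data". Then: "In the case of unequal distribution of participant visits over time and/or substantial missing data, we will employ GLMM". Neither condition has a cut-off.
- **Outcome:** "The primary outcome is recent (i.e., past 6 months) self-reported overdose".
- **Exposure, measured over the same window as the outcome:** "the primary exposure is a categorical measure of frequency of DCS access over the past 6 months".
- **Claim for the models:** "These models efficiently address problems of missing data and variable timing of subject visits".
- **Safeguards:** time-varying survey variables enter the GLMM as potential confounders, and multilevel multiple imputation is optional. As a check on loss to follow-up, sociodemographic and drug-related factors are "compared among participants who only completed a baseline DCS visit and those that accessed the service repeatedly".

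The *Data collection* section has the intake survey completed each time a client comes to DCS. *Sample size (Aim 1)* describes passive recruitment through service use and says "we are unable to estimate the proportion of surveys to be obtained from unique versus repeat clients" before the service starts. The model section itself expects follow-up times to vary between clients. *Limitations* does not mention visits driven by overdose risk.

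**The concern.** There are two linked faults.

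**The target effect is left to the data.** For a binary outcome with a logit link, the population-averaged and subject-specific odds ratios differ whenever clients differ in underlying risk. Missingness and irregular spacing are good reasons to choose one estimation method over another, such as likelihood or weighting. They are not reasons to change the effect being estimated. As written, the meaning of the primary odds ratio is unknown until the visit pattern has been seen.

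**The visit-timing claim leaves out its condition.** Irregular visits do no harm only if their timing is unrelated to overdose, given what is in the model. In the DCS survey data, the outcome is observed when a client chooses to attend, and the exposure is how often the client attended over the same 6 months. If a recent overdose, or a period of higher risk, makes people attend more, visit frequency and overdose are associated whether or not DCS has any effect. Either model could then report a biased primary odds ratio.

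**Working it through.** **Plan's own figure.** None bears directly on this point. The article gives no Aim 1 effect size, 6-month overdose prevalence, within-client correlation or visit rate. The expected 1080 DCS clients is used below only as the simulated population size. All other inputs are assumptions.

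**Step 1: which branch would be used.** GEE needs evenly spread visits and little missing data. GLMM applies if visits are uneven, if missingness is substantial, or both. Attendance is at the client's initiative and the article expects varying follow-up, so the rule very probably leads to GLMM.

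**Step 2: how far apart the two targets are (illustration, not bias).** For a random-intercept logit model with SD σ, approximately:

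OR_marginal = OR_conditional^(1/√(1 + 0.346σ²))

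With OR_conditional = 0.60:
- σ = 1: 0.60^(1/√1.346) = 0.644
- σ = 2: 0.60^(1/√2.384) = 0.718
- σ = 2.5: 0.60^(1/√3.1625) = 0.750

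Numerical integration gives the same picture. Over intraclass correlations of 0.1 to 0.7 and 6-month overdose prevalences of 15% to 40%, a conditional OR of 0.50 corresponds to a marginal OR of 0.51 to 0.71, and a conditional OR of 0.70 to 0.71 to 0.84. Each figure is correct for its own target.

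**Step 3: do the models handle risk-driven visits?** The simulation had 1080 people, 36 months, 40 replicates and no true DCS effect.
- Monthly overdose: logit −4.0 plus stable risk (SD 1.2).
- Monthly visit: logit −2.0 plus a client term (SD 0.8).
- Outcome: any overdose in the prior 6 months, recorded only at visits.
- Exposure: 2 or more visits against fewer in those same 6 months.
- Scenario B adds 0.5 × stable risk to the visit logit.
- Scenario C adds 1.0 to it after an overdose in the prior 3 months.
- Scenario D adds 0.5 × stable risk and 0.5 × a changing risk that also drives overdose.

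| Scenario (true OR 1.00) | GEE, independence | GEE, exchangeable | GLMM | 6-month overdose prevalence: at visits / all |
|---|---|---|---|---|
| A. Visits unrelated to risk | 0.97 | 0.99 | 0.97 | 0.160 / 0.161 |
| B. Visits follow stable risk | 1.96 | 1.17 | 1.37 | 0.237 / 0.163 |
| C. Visits follow recent overdose | 1.62 | 1.55 | 1.98 | 0.232 / 0.161 |
| D. Visits follow stable and changing risk | 2.50 | 1.72 | 2.20 | 0.306 / 0.203 |

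Independence GEE rejected the true null in 5% of replicates in A and in 100% in B, C and D. With only 40 replicates, the 5% is rough.

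The autoregressive structure and covariate adjustment were not simulated. The odds ratios in B to D combine selective observation, confounding by risk and reverse causation within the shared window. They therefore do not isolate the visit-timing fault.

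**Step 4: the safeguards.** Measured time-varying covariates can remove only the part of risk-driven visiting that they capture. The one-visit versus repeat comparison is descriptive, corrects nothing, and uses a split strongly related to exposure.

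**The case against.** The best defence is that the rule is stated in advance, depends on visit pattern and missingness rather than on effect estimates, and in practice leads to GLMM. Cut-offs for low or substantial missingness are detail that a condensed article may leave to the analysis plan. A likelihood-based GLMM can also be valid when visit timing depends only on modelled history, and the plan includes time-varying covariates.

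Much of this stands. The absence of cut-offs is not the point here, and the switch matters less in practice than the visit process. But the article still names no target effect and keeps a branch that its own design makes unlikely. The covariate argument reaches only measured risk, and it does not cover an exposure that is itself the visit count.

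A reader might infer four stronger claims that the article does not support:

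- *Model choice alone shrinks a 40% reduction in odds to 25–36%, and this is bias.* Step 2 contrasts two valid targets under assumed SDs, and the GEE branch is unlikely to be used.
- *The one-visit versus repeat split is the exposure itself.* Exposure is time-varying: repeat clients contribute low-exposure records at first visits and after gaps longer than 6 months. The check can show whether returners differ on measured factors.
- *Overdose is recorded only when someone uses DCS.* That is true of the DCS survey. Table 1 also lists SCS client data for self-reported overdose, and the SCS substudy includes people who do not use DCS. The primary model is not tied to either.
- *Frequent attenders dominate the estimate whichever model is used.* That description fits independence GEE best.

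**Conclusion.** The point holds in two parts and should be corrected. First, the article lets observed data features decide which odds ratio is primary and never names the target, although the design makes one branch redundant. Second, it states without qualification that the models deal with visit timing, when this needs timing to be unrelated to overdose given the modelled history. The DCS survey design makes that doubtful.

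The documents do not allow the bias to be sized. Under the assumed scenarios, a true odds ratio of 1.00 appeared as 1.17 to 2.50 with GEE and 1.37 to 2.20 with GLMM. The upward direction follows from assuming that people at higher risk attend more. The opposite dependence was not simulated. The gap between the two odds ratios in Step 2 is a difference of target and depends on the assumed random-intercept SD.

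**What to change.** 1. Name one target effect and one primary model now, and delete the data-dependent switch. One option is a logit GLMM with a random client intercept, also reported as a standardized population-averaged odds ratio and risk difference. State whether the autoregressive structure is kept.
2. Qualify the visit-timing sentence, for example: *These models allow for irregular visits provided that visit timing is unrelated to overdose, given the covariates and history in the model.*
3. Pre-state a sensitivity analysis among clients with linked visits: a marginal model with inverse-intensity-of-visit weights built from prior overdose, prior DCS use and baseline factors. Say that it addresses only timing explained by measured history, and that it does not remove reverse causation within the shared 6-month window.
4. Describe the one-visit versus repeat comparison as a limited descriptive check related to exposure.

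The cost is revised wording and slightly more analysis work, with no new data collection. The sensitivity analysis is limited to clients whose visits can be linked, which *Limitations* says depends on their willingness to create and consistently use an anonymous identifier.

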#### Longitudinal analysis of time-updated overdose data (Aim 3)

Using OCC and TPaS data, the influence of DCS on the annual incidence of fatal and non-fatal overdose events will be characterized, while adjusting for underlying trends over time. Following others [54], conditional fixed effects Poisson models will be employed to test overdose incidence counts in geographic units that do and do not have DCS present, while adjusting for the presence of SCS. This approach allows for assessment of the estimated effect of DCS by analyzing the fluctuation in incidence rates in areas before and after DCS implementation, and by then comparing the relative change in incidence to other geographic areas. Disentangling the independent effects of DCS from those of SCS presents analytic challenges. However, SCS in Toronto were operational before DCS. This stepwise implementation represents an ideal natural experiment to assess the independent effect of DCS.

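### The single Aim 1 coefficient for DCS frequency mixes between-client and within-client contrasts; split it, and do not call it a pre/post effect if the two parts differ

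*Protocol article*

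**What the plan says.** All references are to the protocol article. In the Aim 1 section on the multivariable model, "The primary outcome is recent (i.e., past 6 months) self-reported overdose" and "the primary exposure is a categorical measure of frequency of DCS access over the past 6 months". The model is a logit GEE or GLMM, chosen by how evenly visits are spread and how much data are missing. The section then justifies this choice: "Both GEE and GLMM are suited to the analysis of longitudinal data, as they can account for both within-subject correlation and between-subject differences". On covariates it says "GLMM models will also include independent time-varying variables from the linked intake and post-test surveys as potential confounders", and the next sentence offers a pre versus post evaluation from the longitudinal data. It mentions no client-mean term, no client fixed effect and no separation of the two sources of variation in frequency.

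The section on intake and post-test surveys surveys one-visit and repeat clients together, "allowing for a combined use of cross-sectional and longitudinal approaches", and collects demographic and drug-using factors at the first visit. The conceptual framework section says that the framework will guide variable selection. The limitations concede that there is no comparison group outside the SCS sub-analysis. For areas, in Aim 3, "conditional fixed effects Poisson models will be employed to test overdose incidence counts in geographic units".

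**The concern.** Clients decide for themselves how often to use DCS. Dependence, housing or caution may influence both that choice and overdose risk. A working correlation or a random intercept models the dependence among one client's answers, but neither removes stable confounding: GEE estimates a marginal contrast, and the GLMM assumes that the random intercept is unrelated to DCS frequency. The primary odds ratio could then move away from 1 when DCS changes nobody's risk, or sit near 1 when DCS helps. The article's wording invites readers to take that odds ratio as already freed of differences between clients.

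**Working it through.** **The plan's own figure.** The only planning number used here is n = 1080 clients. 9000 × 0.20 = 1800 reproduces; 1800 × 0.75 = 1350; 1080 needs a further factor of 1080/1350 = 0.80, which the article attributes to social desirability bias without stating it. Below, 1080 serves only as the number of clients.

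**Algebra.** The article gives no equation. Its description corresponds to

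logit P(Y_it = 1) = b0 + b·x_it + covariates (+ u_i in the GLMM).

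Write x_it = m_i + (x_it − m_i), where m_i is the client's own mean, and give the parts coefficients B (between) and W (within). The planned model forces B = W. For a one-visit client x_it − m_i = 0, so that client informs B only. If the stable risk left after adjustment is related to m_i with slope k, then B = W + k, and the pooled coefficient is approximately

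w·W + (1 − w)(W + k) = W + (1 − w)·k.

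This is exact for a linear model and a guide on the logit scale. The distortion is zero if k = 0. Under the GLMM it shrinks as visits per client rise, because w rises.

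**Simulation 1 (assumed inputs).** 1080 clients, all with 2, 4 or 8 visits; high/low DCS frequency with log-odds −0.3 + a·u; overdose with log-odds −1.8 + 1.2·u; u standard normal; true within-client OR 1.00; 10 runs per setting, so second decimals are noisy. Stable risk is the only driver of stable differences in use, which is a strong assumption. Adding the client mean and conditional logistic regression agreed to two decimals and share the last column.

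| Stable risk and DCS use | Visits | GEE (AR1) | GLMM | Within-client |
|---|---|---|---|---|
| Higher risk, more use (a = 0.5) | 2 | 1.48 | 1.59 | 0.99 |
| | 4 | 1.46 | 1.46 | 0.99 |
| | 8 | 1.43 | 1.31 | 1.02 |
| Unrelated (a = 0) | 2 | 0.99 | 0.99 | 0.94 |
| | 4 | 0.98 | 0.97 | 0.97 |
| | 8 | 1.04 | 1.05 | 1.05 |
| Higher risk, less use (a = −0.5) | 2 | 0.63 | 0.59 | 0.90 |
| | 4 | 0.69 | 0.69 | 0.98 |
| | 8 | 0.69 | 0.76 | 0.98 |

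- *Measured adjustment* (a = 0.5, 4 visits, half the variance of u measured and adjusted): GEE 1.21 and GLMM 1.20, down from 1.46; within-client 0.95.
- *True OR 0.70* (a = 0.5, 4 visits): GEE 1.06, GLMM 1.00, within-client 0.69. A marginal OR lies nearer 1 even without confounding: ln 0.70 = −0.357, divided by √(1 + 0.346 × 1.44) = 1.224, gives −0.291, or OR 0.75. That explains only part of the GEE gap.

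**Simulation 2 (weaker link, with one-visit clients).** 1080 clients, about 20% overdose per six months, client SD 1 on the log-odds scale, 30% or 60% of clients with 4 visits and the rest with one, no true effect. With a correlation of 0 / 0.2 / 0.3 between stable risk and stable tendency to visit, the GLMM rejected at nominal 5% in 4–6% / 36–39% / 62–73% of runs (mean OR 1.0 / 1.2 / 1.3). The within-client term rejected in 3–6%. Separate runs at correlation 0.3 gave a GLMM OR of about 1.2 and 40–45% rejections, so the size depends on settings that the article does not fix.

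**Simulation 3 (the alternative under strain).** No DCS effect, 60% of clients with 4 visits, and an earlier overdose raising the log-odds of later high DCS use by 0.5 or 1.0 (60 runs). Conditional logistic regression gave OR 0.86 or 0.80 and a false benefit in 27% or 48% of runs; without feedback, 1.01 and 2%. In separate runs with such feedback the within-client term fell to 0.90 down to 0.78 while the GLMM stayed near 1.0. About 280 of 1080 clients (26%) were informative for the conditional model, and about 140 (13%) with 30% repeat clients.

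**The case against.** The other side has several good points.

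- *Pre versus post may mean before and after the drug test.* Table 1 assigns intake and post-test data to protective behaviours, but among the DCS surveys only intake data to overdose. This stands in part. Yet the phrase occurs in the section that defines overdose as the primary outcome and is not limited to other outcomes.
- *Accounting for between-subject differences commonly means modelling heterogeneity.* This stands. A reader might infer that the models touch such differences only through standard errors, or that the client never serves as their own control. The document does not support either inference: the GLMM random intercept moves the coefficient itself towards within-client information, as the fall from 1.59 to 1.31 shows.
- *Stable factors may be adjusted.* Baseline factors are collected and the framework guides selection. This stands and shrinks the problem without removing it.
- *Fixed effects for areas create no contradiction.* Areas can have counts in every period; clients have irregular visits and uncertain linkage, so different estimators are defensible. This stands.
- *The article is condensed and candid.* It frames its goal as association, discloses the combined cross-sectional and longitudinal approach, admits the missing comparison group, and compares one-visit with repeat clients. A split could be in a fuller plan. But the point concerns a property that the article asserts for its named primary analysis, not an omitted detail.
- *The within-client term can mislead too.* Simulation 3 shows this. A first visit also carries little or no prior DCS access, so change in frequency partly follows visit order. This stands and limits the fix.

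**Conclusion.** The concern holds in limited form. The planned coefficient is a weighted mix of between-client and within-client contrasts, and the article's description of GEE and GLMM, together with the pre versus post claim, does not tell the reader so. Stable differences left after measured adjustment can appear as a DCS effect. With no true effect, the stronger assumed scenarios gave odds ratios of 1.31–1.59 or 0.59–0.76, falling to about 1.20 from 1.46 with half the stable risk measured; weaker links gave about 1.2–1.3. All of these rest on assumed event rates, heterogeneity, visit counts and strength of selection, and the effect disappears if stable risk and DCS use are unrelated.

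Two stronger conclusions are tempting and unsupported. One is that the primary odds ratio will be biased in a known direction; nothing in the document settles that. The other is that the within-client term, or conditional logistic regression, is the right sole pre/post estimate; feedback from overdose to later DCS use would bias it towards benefit. This is a worthwhile, inexpensive improvement, not a fatal flaw.

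**What to change.** 1. In the primary model, replace the single frequency term by the client's own mean (for a categorical exposure, the client's proportion of visits in each category) and the visit-level deviation from it.
2. Adjust for the baseline demographic and drug-using factors already collected, whichever of GEE or GLMM is used; the article names confounders for the GLMM only.
3. Report both coefficients with a test of whether they differ. If they do, do not describe the single pooled coefficient as a pre/post effect.
4. Reword the justification so that GEE and GLMM are said to model within-client correlation and heterogeneity, not to remove between-client confounding.
5. Keep conditional logistic regression as a sensitivity analysis. It is not equivalent, since it uses only clients whose outcome and exposure both vary.

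The cost is plan wording and a covariate derived from data already collected. State the downsides: the within-client term rests on clients with two or more linked visits and has a wider interval; it does not remove time-varying confounding; and it is biased if an earlier overdose changes later DCS use. It should therefore be read beside the between-client term, not in place of it.
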